## Abstract

**Background:**

Older adults are the fastest growing segment of the world‘s population. Recent evidence indicates that excessive sitting time is harmful to health, independent of meeting the recommended moderate to vigorous physical activity (PA) guidelines. The SITLESS project aims to determine whether exercise referral schemes (ERS) can be enhanced by self-management strategies (SMSs) to reduce sedentary behaviour (SB), increase PA and improve health, quality of life and function in the long term, as well as psychosocial outcomes in community-dwelling older European citizens from four countries, within a three-armed pragmatic randomised controlled trial, compared with ERS alone and also with general recommendations about PA.

**Methods:**

A total of 1338 older adults will be included in this study, recruited from four European countries through different existing primary prevention pathways. Participants will be randomly allocated into an ERS of 16 weeks (32 sessions, 45–60 min per session), ERS enhanced by seven sessions of SMSs and four telephone prompts, or a control group. Outcomes will be assessed at baseline, month 4 (end of ERS intervention), month 16 (12 months post intervention) and month 22 (18 months post intervention). Primary outcomes will include measures of SB (time spent sedentary) and PA (counts per minute). Secondary outcomes will include muscle and physical function, health economics’ related outcomes, anthropometry, quality of life, social networks, anxiety and depressive symptoms, disability, fear of falling, executive function and fatigue. A process evaluation will be conducted throughout the trial. The full analysis set will follow an intention-to-treat principle and will include all randomised participants for whom a baseline assessment is conducted. The study hypothesis will be tested with mixed linear models with repeated measures, to assess changes in the main outcomes (SB and PA) over time (baseline to month 22) and between study arms.

**Discussion:**

The findings of this study may help inform the design and implementation of more effective interventions to reduce SB and increase PA levels, and hence improve long-term health outcomes in the older adult population. SITLESS aims to support policy-makers in deciding how or whether ERS should be further implemented or restructured in order to increase its adherence, impact and cost-effectiveness.

**Trial registration:**

ClinicalTrials.gov, NCT02629666. Registered 19 November 2015.

**Electronic supplementary material:**

The online version of this article (doi:10.1186/s13063-017-1956-x) contains supplementary material, which is available to authorized users.

## Background

Older adults are the fastest growing segment of the world’s population [1]. Although prolonging life remains an important public health goal, of even greater significance is the preservation of functional and cognitive performance, and of the capacity to live independently during late life.

Being insufficiently active is associated with increased risk for major non-communicable diseases and all-cause mortality, which is related to increased healthcare costs [2–4]. It is estimated that people aged 65 years and over account for 30–40% of the total healthcare spend across Europe [5]. The burden of disease attributable to being insufficiently physically active has recently been estimated to be responsible for 6–9% of the total deaths worldwide and accounts for as many as 5.3 million deaths per year [2, 6]. In this context, it is estimated that across all ages, 31% of the global population do not meet current physical activity (PA) recommendations established by the World Health Organization (WHO) [7].

In the last decade, growing evidence indicates that excessive sitting time may be harmful to health, independent of meeting the recommended moderate-to-vigorous PA guidelines [8–13]. Time spent in sedentary behaviour (SB)—defined as any waking behaviour characterised by energy expenditure ≤ 1.5 Metabolic Equivalent Tasks (MET) while in a sitting or reclining posture [14]—has increased substantially over the last three decades [15]. Older adults are the most sedentary segment of society, as many spend over 75% of their waking day in SB [16]. Current evidence suggests that prolonged SB is associated with increased rates of several chronic diseases and all-cause mortality in older adults [17–20].

Primary care is a key setting for the promotion of PA. The most common model of PA promotion in primary care involves exercise referral schemes (ERS), whereby a general practitioner or another member of the primary care team (e.g. physiotherapist, nurse or pharmacist) identifies and refers insufficiently active individuals to a third-party service (often a sports centre or leisure facility) to conduct an exercise program [21, 22]. Despite recent studies showing the health benefits of such programs, most studies also demonstrate that such gains are rarely sustained [21]. Recent guidelines also advocate the use of established behavioural change techniques (BCTs) to promote increased levels of PA [23]. Among those, self-management strategies (SMSs) may successfully improve involvement in exercise in specific populations, increasing levels of daily PA, enhancing quality of life, improving mental health, producing greater confidence and increasing power to act [24].

Research focusing on interventions to reduce SB has only begun to emerge in the last five years and there have been few studies conducted in older adults. Recent studies targeting reduced SB in this population have included BCTs such as goal setting, instruction on how to perform the behaviour, self-monitoring and feedback of behaviour, prompts/cues and restructuring the physical environment [25–29]. Moderate quality evidence indicates that specific interventions have the potential to reduce SB in older adults [30]. These findings are supported by systematic reviews focusing on adults [31–33]. As far as we know, no previous studies have assessed the effects of an exercise-based intervention enhanced by SMSs addressing both increased daily PA and a reduction of SB in older adults.

Therefore, the SITLESS project aims to determine whether ERS can be enhanced by SMSs to reduce SB, increase PA and improve health, quality of life and function in the long term (22 months), as well as psychosocial outcomes in community-dwelling older European citizens from four countries, within a three-armed pragmatic randomised controlled trial (RCT), compared with ERS alone and also with general recommendations about PA. SITLESS will also collect health economics’ related outcomes, data on healthcare systems and community costs to perform cost-effectiveness analyses. SITLESS has the purpose to support policy-makers in deciding how or whether ERS should be further implemented or restructured in order to increase its adherence, impact and cost-effectiveness.

## Methods/design

### Study design

The present study protocol describes a multi-centre pragmatic three-armed parallel RCT. Outcomes will be assessed at baseline, month 4 (end of intervention), month 16 (12 months post intervention) and month 22 (18 months post intervention) which will be the main outcome assessment. The study protocol has been developed based on the Standard Protocol Items: Recommendations for Interventional Trials (SPIRIT) guidelines [34]. The study design was approved by the Ethics and Research Committee of each intervention site: The Ethics and Research Committee of Ramon Llull University (Fundació Blanquerna, Spain), The Regional Committees on Health Research Ethics for Southern Denmark (University of Southern Denmark, Denmark), Office for Research Ethics Committees in Northern Ireland (ORECNI) (Queen’s University of Belfast) and the Ethical Review Board of Ulm University (Ulm, Germany). Participation is voluntary and all participants will be asked to sign informed consent before the start of the study (see Additional file 1).

SITLESS, as a Responsible Research and Innovation project, has created guidance for the involvement of stakeholders in the project from the onset. Accordingly, four local advisory boards were created, one on each intervention site (Barcelona, Odense, Belfast, Ulm) and are periodically involved in the study. They comprise primary healthcare and sport professionals, older adults, policy-makers and other local stakeholders of relevance (e.g. health insurance, where relevant). A gender expert linked to the European project EGERA is part of the advisory board of Barcelona.

### Participants

A total of 1338 participants (randomised into three intervention groups of 446 participants) will be included in this study and recruited in four intervention sites (Barcelona, Odense, Belfast, Ulm). Each intervention site will be in charge of recruiting 335 participants and will collect relevant descriptive information regarding participants’ demographic characteristics (e.g. age, gender, marital status, living arrangements and educational background). Barcelona is the largest site of the study with 1,602,000 inhabitants in 2014, followed by Belfast with 333,871 at the 2015 census. Odense and Ulm have less than 200,000 inhabitants. Outcome measures will be also analysed to detect any between-site differences.

Participants are eligible if they are: (1) aged 65 years or above; (2) community-dwelling; (3) able to walk without the help of another person for at least 2 min with or without a walking aid; (4) have no major physical limitations as shown by a score on the Short Physical Performance Battery (SPPB) of 4 or above [35]; (5) insufficiently active as determined by the following screening question: ‘*Do you perform regular physical activity (PA) for at least 30 minutes five or more days of the week (referring only to PA that makes the participant become out of breath while doing it or such that it doesn’t allow him/her to maintain a conversation while doing the activity) (do not count regular walking)*’; and/or (6) report spending long periods of time in SB by answering affirmatively to the question: ‘*For most days, do you feel you sit for too long (6–8 hours or more a day)? Some examples might include when watching TV, working at the computer / laptop or when doing sitting-based hobbies such as sewing*’ [17]. Participants will be excluded if they: (1) have moderate or severe dementia when screened with the six-item screener to identify cognitive impairment, using a cutoff of three or more errors [36]; (2) have a medical condition which may interfere with the study design; (3) have unstable medical conditions (e.g. elevated blood pressure after medication, uncontrolled hypertension) or symptomatic cardiovascular diseases that contraindicates participation in PA; (4) expect not to be able to attend 75% of the ERS sessions throughout the intervention; and (5) have participated in an ERS in the six months prior to their entry into the study.

### Sample size

A sample size of 1338 participants (randomised to one of three groups of 446 participants) will be needed to detect a moderate effect size of 30 daily counts per minute (CPM) in a two-sided test, at a power of 80% and an α of 0.05, a common standard deviation of 139 of the mean and a 24% dropout rate. A change of 30 CPM is considered a measurable moderate effect size in this population, assessed with ActiGraph GT3X+, and 139 is the standard deviation for CPM found in the literature [37]. The present sample size allows estimation of overall efficacy.

Sample size computations were conducted with online software GRANMO (http://www.imim.es/ofertadeserveis/software-public/granmo/; last accessed on 21/7/2014).

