No subgroup analyses are planned in advance. Any subgroup analysis conducted will be treated with caution and output will be treated as exploratory rather than definitive. Missing data will be imputed through a multiple imputation approach, imputing missing values with the corresponding average values from the set of participants in the control group in the same country as the participant, matched for age, gender, baseline PA and baseline SPPB score.

Two-sided tests of statistical significance will be used in all statistical analyses. Estimates of the size of treatment effects will be presented together with confidence intervals, in addition to significance tests. Significance levels will be set to a 5% level, applying the Bonferroni correction to adjust for type I error criteria. All analyses will be performed with SPSS version 20 or Stata version 12.

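### The 80% power for 30 CPM is calculated at an uncorrected 0.05, while the analysis applies Bonferroni, so the stated power does not describe the planned tests

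*Protocol article*

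**What the plan says.** The Sample size section sets 1338 participants, 446 in each of three arms. The target is a difference of 30 CPM, tested two-sided; the remaining inputs are "at a power of 80% and an α of 0.05, a common standard deviation of 139 of the mean and a 24% dropout rate". It mentions no adjustment for multiple tests.

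The Data and statistical analysis section names two main outcomes, SB and CPM, compared between the arms from T0 to T3 by a repeated-measures mixed linear model. It ends with the rule "Significance levels will be set to a 5% level, applying the Bonferroni correction to adjust for type I error criteria". The number of tests in the correction is not given.

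The Abstract and the last paragraph of the Background state the aim as two comparisons: ERS + SMS against ERS alone, and ERS + SMS against general recommendations on physical activity (the control arm). The Study design section makes month 22 the main outcome assessment.

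**The concern.** Power belongs to a particular test at a particular significance level. The sample size is justified "at a power of 80% and an α of 0.05", but a Bonferroni correction over two or more tests means that no single test is run at 0.05. Unless the family has only one member, in which case the correction does nothing, the two sections cannot both describe the same test.

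The stake is how a non-significant result is read. ERS + SMS against ERS alone is the distinctive question of the trial and is meant to inform policy on exercise referral. If that contrast is null, readers will weigh it against a stated 20% chance of missing a true 30 CPM difference. At the corrected level, under the same assumptions, that chance is larger.

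**Working it through.** **Inputs, all from the Sample size section:** difference 30 CPM; SD 139; two-sided α 0.05; power 80%; dropout 24%; 446 per arm.

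**1. Reproduce the plan's figure.**

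n per arm = 2 × (1.960 + 0.842)² × 139² / 30² = 337 evaluable.

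337 / (1 − 0.24) = 444 per arm, 1332 in total, against the stated 446 and 1338. The agreement is close, so the basis is one two-mean comparison of one outcome at an uncorrected 0.05.

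**2. Standard error with the stated enrolment.**

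446 × 0.76 = 339 evaluable per arm. SE = 139 × √(2/339) = 10.68, and 30 / 10.68 = 2.81.

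**3. Power and detectable difference for k tests under Bonferroni.**

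Power = Φ(2.81 − z), where z is the normal quantile at 1 − 0.05/(2k). Difference detectable with 80% power = (z + 0.842) × 10.68.

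| Family | k | Level | z | Power for 30 CPM | Detectable difference (CPM) |
|---|---|---|---|---|---|
| One contrast, CPM | 1 | 0.05 | 1.960 | 80.2% | 29.9 |
| Two stated contrasts, CPM | 2 | 0.025 | 2.241 | 71.5% | 32.9 |
| Two stated contrasts, SB and CPM | 4 | 0.0125 | 2.498 | 62.3% | 35.7 |
| Three pairwise contrasts, CPM | 3 | 0.0167 | 2.394 | 66.1% | 34.5 |
| Three pairwise contrasts, SB and CPM | 6 | 0.0083 | 2.638 | 56.8% | 37.2 |

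The last two rows add ERS against control, which is not among the stated aims. Using the t distribution changes little: 71.3% for two tests and 56.5% for six.

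**4. Could a global three-arm test explain the stated size?**

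The Sample size section refers to overall efficacy. With 339 per arm, a three-arm F test at 0.05 has 71.0% power for arm means 0/15/30 and 83.5% for 0/0/30. Neither gives the stated 80%, whereas the single two-arm comparison does.

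**5. What baseline adjustment could recover.**

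The document gives no correlation between baseline and follow-up CPM, so r is an assumption here. Adjusting for baseline multiplies the SE by √(1 − r²). For four tests, power = Φ(2.81/√(1 − r²) − 2.498):

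| Assumed r | Power, four tests |
|---|---|
| 0 | 62.3% |
| 0.3 | 67.3% |
| 0.5 | 77.2% |
| 0.6 | 84.5% |
| 0.7 | 92.5% |

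These figures are before any loss from clustering of couples or exercise groups.

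**The case against.** The strongest objection is that the planned test is not an unadjusted two-sample comparison. A repeated-measures mixed model may use baseline and earlier visits. With a high enough correlation, power could exceed 80% even at the corrected level, as the second table shows. This stands as a limit on the claim. A reader might infer that the trial's real power is 57% to 72%; the document does not support that, because those figures hold only under the Sample size section's own assumptions. Nor does the objection restore the stated 80%. The Sample size section takes no credit for repeated measures. The analysis section considers a diagonal within-participant covariance, and its listed covariates (age, gender, BMI, SPPB level and frailty) do not include baseline CPM. Clustering works in the other direction.

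A second objection is that defining the family is commonly left to the statistical analysis plan. That also stands: an unnamed family is not a fault by itself. The conflict remains because every family of two or more tests contradicts the stated power.

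Two further readings go too far. A reader might take the correction to span every analysis in the trial, but the wording about all analyses belongs to a separate sentence on two-sided testing; the Bonferroni sentence names no scope. A reader might also take 66.1% or 56.8% as the figure to print, but both require the ERS against control contrast, which the stated aims do not include.

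**Conclusion.** The point holds as an inconsistency between two sections. It is not an arithmetic error: 446 per arm is right at its own inputs. Under those inputs (SD 139, 24% dropout, 339 evaluable per arm, two-sample comparison), the two stated contrasts on CPM have 71.5% power each. With SB included in the family, power for a CPM contrast is 62.3%. The chance of missing a true 30 CPM difference is then about 28% or 38%, against the 20% implied, and the difference detectable with 80% power is 32.9 or 35.7 CPM. If ERS against control joins the family, power is 66.1% or 56.8%.

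The power of the mixed model itself cannot be computed from the document, because no correlation or clustering figure is given. It does not follow that the trial must be enlarged; what must change is the statement of power.

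**What to change.** Reconcile the Sample size section with the Bonferroni sentence:

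- Name the primary family: which contrasts, which outcomes, and month 22 as the time point.
- Restate power for 30 CPM, and the difference detectable with 80% power, at the resulting level. The rows of the first table in the working can be used directly.
- If credit is taken for baseline adjustment, add baseline CPM to the model in the Data and statistical analysis section. Show power over a range of assumed correlations and say how clustering of couples and exercise groups is allowed for. This changes the model as well as the wording.

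The first two steps need no further participants; the cost is a less favourable stated power. The Trial status section reports fewer than 250 participants included and none through the intervention at submission, so at that stage the change could be made before outcomes were known.

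A fixed-sequence procedure, testing each step at the full 0.05, is an alternative open to the sponsor. It is a design choice, not a correction, and makes later claims depend on earlier ones.

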### Study procedure

Recruitment strategies will be site-specific according to the different existing primary prevention pathways in each country. Primary care centres and other health-related centres of each intervention site will be informed and asked to participate. The research team will inform professionals about the background and the aims of the study. Health professionals who volunteer to participate will be further given all information regarding eligibility criteria and the recruitment strategy. Posters, flyers, newspapers, radio broadcasts and social media outlets will also be used to advertise the study and as additional recruitment strategies (Additional file 2: shows the SPIRIT checklist).

Health professionals or the local research team will assess interested individuals against the eligibility criteria. Eligible participants will have their name, gender, date of birth and phone number recorded, while individuals deemed ineligible or that do not want to participate will have their reason for declining as well as their gender and age recorded.

### Randomisation and blinding

During the first meeting, a researcher will explain the trial to interested individuals, give them an information sheet about the study and obtain their written informed consent (see Additional file 1). Participants will then be scheduled for the baseline testing session. After the baseline assessment, each participant will be centrally randomised to one of the three study groups (e.g. ERS + SMS, ERS or the control group), using a computer-based random-block randomisation scheme, clustering by couples when cohabitees wish to be enrolled together. Concealed randomisation will be conducted centrally at FSiE, after each participant has been included in the study, assigned an identification code and has completed the study baseline assessment.

The trial has an open design with blind assessment of outcomes. Researchers conducting the baseline assessments will be blind to group allocation. The statistician will also be blind to group allocation until completion of the statistical analysis. Participants will be asked not to reveal group allocation when undergoing follow-up measurements, as researchers conducting follow-up measurements will be blind to group allocation. To assess the extent to which blinding has been preserved, researchers will record the number of cases in which allocation was revealed.

### Study interventions

A complex intervention [38] consisting of a PA program with self-management strategies (ERS + SMS) will be delivered in primary care or community settings in urban areas of Barcelona (Spain), Odense (Denmark), Belfast (UK) and Ulm (Germany) (see Table 1). All trainers in charge of conducting both intervention groups will undergo a standardised training.

**Table 1 Tab1:** General information of the ERS and SMS interventions

Name of the program	Program components	Training responsible	Duration	General structure of each session
ERS intervention	Aerobic training. Strength-based/ endurance exercises. Balance-based functional exercises. Flexibility exercises.	Specially trained PA specialist: physical therapist; sport professional/trainer; ergotherapist with specific health qualification. Sessions will be always performed under the supervision of the same trainer.	16 weeks. Two sessions per week of 45–60 min. Ask each participant to perform a third session on their own such as a 30-min walk. The intervention will be conducted in an indoor primary-care or sports facility. Municipality facilities (e.g. activity centres for older adults).	All training sessions will begin with a 5–10 min warm-up focusing on social and physical interactions. Followed by 35 min of different exercises adapted to each individual’s functional level (according to the participants’ SPPB score^a^). All training sessions will end with cool-down (breathing exercises and stretching for 5–10 min.
SMS intervention	Raising awareness on differences, associations, risks and benefits of SB and PA. Setting personal activity goals (long-term achievement goals). Enhancing motivation. Goal-setting focusing separately on SB and PA. Self-monitoring (pedometer and activity diary). External monitoring (instructor). Problem-solving according to the IDEA.^b^ Social influence and social support. Raising awareness on facilitators and barriers of PA and SB at home and neighbourhood. Environmental signposting.	The same specialist for the ERS intervention.	Total of 30 weeks. 1 one-to-one session (week 1; 40 min). 6 group-based sessions (weeks 3, 4, 5, 7, 9 and 11; 45–60 min). 4 telephone calls (weeks 15, 20, 25 and 30; 20 min).	The SMS sessions include the following activities: introducing the project to the participant, developing a rapport, setting a meaningful long-term goal to be achieved at the end of the intervention, identifying facilitators and barriers of PA and SB at home and neighbourhood in a group dynamic, environmental signposting to help engaging participants in local opportunities to do PA, checking daily step counts registered in the activity diary and setting individual goals to increase steps or other physical activities, setting individual goals to reduce siting time set choosing recommendations (SITLESS tips) for decreasing SB, problem-solving techniques to overcome barriers to being less sedentary and more active according to the IDEA^b^ problem-solving.

^a^Total SPPB score ranges from 0 (worst performance) to 12 (best performance); participants will be classified into three different functional performance levels according to the results obtained: low = 4–6; medium = 7–9; high functional level = 10–12 points

^b^
*IDEA* Identifying the problem, Develop a list of solutions, Evaluate the solutions and Analyse how the plan worked

